### Blinding

Because this is a dietary intervention study, it is not possible for participants or all study personnel to be blinded to group assignment. The study will be assessor-blinded, as the study research nurses who will perform the data collection (e.g. anthropometrics and blood pressure), and the technicians measuring gut microbiota and laboratory works will be blinded to intervention assignment. Moreover, the MRI images will be presented to the investigator anonymously (study identification number only) for analysis.

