### Randomisation and treatment allocation

Randomisation will be performed after written informed consent and screening, when a participant is eligible based on the eligibility criteria. Participants will be randomised to receive the FMD in addition to usual care or usual care only. To ensure equal allocation of subgroups, stratification will be performed for gender and for weight < 100 kg and > 100 kg at baseline. Randomisation will be performed using permuted block randomization with blocks sizes 2 and 4.

Treatment allocation is computer generated via the electronic trial database in Castor EDC [24]. Allocation sequence is concealed by Castor EDC until randomisation of a participant. Castor EDC is used to assign participants to the different groups.

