**Fasting blood sample**										
HbA1c	X	X				X				X
Glucose	X	X	X		X	X	X		X	X
Creatinin	X									
ASAT	X									
ALAT	X									
Haemoglobin	X									
Red cell indices	X									
Leucocytes	X									
Thrombocytes	X									
OGTT (5x glucose and 5x insulin)		X				X				X
Total cholesterol		X				X				X
Low-density lipoprotein (LDL)		X				X				X
High-density lipoprotein (HDL)		X				X				X
Triglycerides		X				X				X
High sensitive CRP		X				X				X
Metabolomics		X								X
IGF-1^a^		X	X		X		X		X	
Insulin-like growth factor-binding protein (IGF-BP-1)^a^		X	X		X		X		X	

Laboratory tests with a ^a^ will only be performed in the FMD group

In compliance with the GCP guidelines, the investigator will store all source documents that support the data collected from each subject, as well as all essential study documents. Source documents include paper case report forms (CRFs), Castor EDC (eCRFs) and Hix ChipSoft (Electronic Health Records Software used in the LUMC). Participant specific data will be labelled with a study identification number and entered in the electronic trial database in Castor EDC. The study identification number will be linked to personal information of the participant used for trial logistics in a separate electronic study database, which will be safeguarded by the investigator in accordance with GCP rules.

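### Labelling MRI scans with the study identification number does not by itself secure blinding of the MRI reader to treatment arm

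*Protocol article*

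**What the plan says.** All references are to the protocol article.

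- **Blinding.** The section concedes that "it is not possible for participants or all study personnel to be blinded to group assignment". It then describes the study as assessor-blinded because the research nurses who collect data and "the technicians measuring gut microbiota and laboratory works will be blinded to intervention assignment". A further sentence deals with imaging: "the MRI images will be presented to the investigator anonymously (study identification number only) for analysis".
- **Data collection (text below Table 2).** On how records are filed, the section says: "Participant specific data will be labelled with a study identification number and entered in the electronic trial database in Castor EDC". The next sentence sets up a second database, kept apart from the first, that ties the number to the person. Its custody is given to a single role; it is a database "which will be safeguarded by the investigator in accordance with GCP rules".
- **Randomisation and treatment allocation.** "Castor EDC is used to assign participants to the different groups".
- **Table 2, footnote.** IGF-1 and IGF-BP-1 are measured in the diet arm only.
- **Incidental findings.** Important findings noticed while MRI scans are being analysed go to the participant and the GP.

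**The concern.** A label hides the arm from a reader only if the reader cannot get from the label to the arm. Here the label is the number under which the rest of the participant's trial data are filed. The article uses one role word for the person who reads the scans and the person who keeps the link to identity. It also accepts that some study personnel know the allocation, and it does not place the MRI reader on one side of that line or the other.

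At stake are the MRI secondary outcomes: visceral fat, liver and heart fat, total body fat, and cardiovascular function. Where a measurement calls for reader judgement, knowledge of the arm could shift it. The article's title, design section and conclusion all describe the trial as assessor-blinded, so the masking method it states for these outcomes should be able to support that description.

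**Working it through.** The plan gives no figure to reproduce for this point. The check is a comparison of the sections, one link at a time.

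1. **Are the images anonymous?** Not strictly. Blinding has them carry the study identification number, and Data collection links that number to personal information. Incidental findings needs someone to be able to trace a scan back to a person. The images are pseudonymised.
2. **Is the reader said to be blinded to assignment?** Nurses and technicians are, in those terms. The MRI sentence says only how images are labelled.
3. **Can the number lead to the arm?** There are three possible routes.
   - Allocation field: data in Castor carry the number and Castor assigns groups. A user with sufficient rights could look up the arm. The article does not say that allocation is keyed or displayed by this number, or that the MRI reader has such rights.
   - Diet-arm-only data: if IGF-1 and IGF-BP-1 results are filed under the number, as the general rule for participant data implies, their presence shows the arm even with the allocation field hidden.
   - Identity: the linking database turns the number into a person. The arm then follows only for someone who knows or looks up that person's group. Data collection has researchers telephone participants in the diet group, and Medication use has the research team draw up safety plans for diet-group participants who start additional glucose-lowering drugs. Neither section says whether the MRI reader is among them.
4. **Is the reader separated from these routes?** No section says so. No section says the opposite either.
5. **How many readings are concerned?** MRI is scheduled at baseline, 6 months and 12 months (T0, T4, T8). The maximum is 100 × 3 = 300 scans. If the 10% loss in the Power calculation falls entirely at T8 and nobody misses T4, the count is 100 + 100 + 90 = 290. These are counts of scans exposed to the weakness, not a measure of bias.
6. **How large could the bias be?** It cannot be derived. The Outcomes section names a liver imaging product and heart spectroscopy and says fat volumes will be quantified, but it does not say how much of any reading is manual. A distortion that was the same at baseline and follow-up would also cancel in a comparison of changes.

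**The case against.** The best case for the plan has four parts.

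- **Coded images are a usual masking device.** The parenthesis in the Blinding sentence itself explains what is meant by anonymous, and the section opens by calling the study assessor-blinded. This stands as a description of intent. The device works, however, only where the reader cannot open the records behind the code, and the article does not say that.
- **The link is to identity, not to arm.** It is a confidentiality measure kept apart from the data. This is correct, and it is why the link alone proves nothing about unblinding.
- **The investigator is a generic role.** The same word is used for eligibility discretion and for withdrawals, so the scan reader and the link-keeper may be different people. This also stands: the shared term leaves the separation unstated but does not show that it is absent.
- **Access rights are detail that an article leaves to the full protocol.** This is fair for access rights as such. The point here is narrower: the article does state its masking method for MRI, and that method hides the name without by itself hiding the arm.

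A reader might go further and infer that the MRI reader is unblinded, or that all MRI results will be biased towards the diet by some percentage. The documents support neither. Nothing says that the number encodes the arm, that the reader opens Castor or the link, or that the reader telephones participants. Nor is there any basis for assuming that every MRI measure depends on manual contouring.

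**Conclusion.** The point holds in a limited form: blinding of the MRI reader is not secured by the labelling the article describes. This rests on three things that can be read directly: the label is the study identification number, the reader is not said to be blinded to assignment as other assessors are, and no section separates the reader from allocation, from diet-arm-only data or from the identity link.

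Actual unblinding is not shown and would require the reader to have, and use, one of those routes. The exposure is confined to the MRI secondary outcomes, with 300 scans as the ceiling and no estimable bias. The combined HbA1c and medication endpoint is not affected. The change is worth making because it is cheap and would let the assessor-blinded description stand for MRI as well.

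**What to change.** **Preferred.** Before reading, existing data-management staff replace the study number on each scan with a random reading code unrelated to it. They hold the code list and re-link the results to the trial database only after the readings are locked. A reader who sees an important incidental finding reports it under the reading code to the code-holder, who identifies the participant so that the notification described under Incidental findings can proceed without unmasking the reader.

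**Minimum.** State in the Blinding section that MRI scans are read only by someone who is blinded to assignment, has no participant contact, and has no access to the Castor allocation, to the IGF-1 and IGF-BP-1 data, or to the linking database.

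**Cost.** The preferred version adds a relabelling step, a code list and a re-linking step. The minimum version needs a sentence in the protocol and matching access rights. Neither changes anything for participants.

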### Data collection

Data collection will be performed by study research nurses at baseline and follow-up visits at the LUMC. All study nurses have received training on how to perform the data collection during the study visits. Follow-up time is 1 year. Participants come in for more extensive visits at study baseline, after 6 months and after 12 months. Furthermore, participants are seen several times in between the extensive study visits. For a detailed timeline of assessments, see Fig. 1. For details on the assessments during the study visits, see Table 2. Participants in the FMD group will receive a telephone call from the researchers during the FMD period, to promote participant compliance to the diet. If applicable, adverse events are recorded.

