**Fig. 1 Fig1:**
[figure not shown]
Timeline of assessments from T0 (baseline) to T8, also in relation to the timing of the FMD

**Table 2 Tab2:** Detailed schedule of assessments during follow up

Follow up	Screening	Baseline	In the first month	In the second month	In the fourth month	After six months	In the eighth month	In the tenth month	In the twelfth month	After twelve months
		T0	T1	T2	T3	T4	T5	T6	T7	T8
**Participant characteristics**	X									
**Medical history**	X									
**Anthropometrics**	X	X	X	X	X	X	X	X	X	X
**Blood pressure**	X	X	X	X	X	X	X	X	X	X
**Medication dosage**	X	X				X				X
**Adverse Events**		X				X				X
**Serious Adverse Events**		X	X	X	X	X	X	X	X	X
**MRI**		X				X				X
**Stool sample (including registration form)**		X	X			X				X
**Finger-stick ketone bodies test**		X	X		X		X		X	

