### Safety

#### Adverse events

Previous experience with this FMD did not reveal serious side effects. Some weakness and headache were sometimes reported. Very few participants dropped out of previous studies because of physical side effects [20, 21]. Hypoglycaemia is not very likely to occur when participants use the FMD while also using metformin, since metformin has no effect on insulin secretion. Metformin will therefore be continued during the FMD. GPs are asked to inform the research team about Serious Adverse Events (SAEs) and Adverse Events (AEs). Participants will be asked at every visit about SAE’s. AE’s will be recorded at several study visits (see Table 2) and during telephone contacts with the research team.

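### Non-serious adverse events have an extra, unblinded recording route in the FMD arm only, so a descriptive between-arm comparison of them would lean towards more events under FMD

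*Protocol article*

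**What the plan says.** Table 2 of the protocol article ("Detailed schedule of assessments during follow up") has separate rows for the two kinds of event. The row "Adverse Events" is marked at T0, T4 and T8. The row "Serious Adverse Events" is marked at T0 and at every visit from T1 to T8. Neither row is restricted by arm; the table's only arm restriction is on the IGF-1 and IGF-BP-1 tests.

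The Data collection section adds a telephone contact for one arm: "Participants in the FMD group will receive a telephone call from the researchers during the FMD period". The stated purpose is to support adherence to the diet. The next sentence reads "If applicable, adverse events are recorded". The Adverse events section under Safety confirms that the calls are a data route, since AEs "will be recorded at several study visits (see Table 2) and during telephone contacts with the research team". The same section states "Participants will be asked at every visit about SAE" (that is, about serious events), and it asks general practitioners to report both serious and non-serious events, without distinction by arm.

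No call to control participants is described. The number of calls per FMD participant is not given.

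**The concern.** The two arms share the visits and the general practitioner route. The FMD arm has in addition a call on diet days, made by staff who must know the allocation because the call is about the diet. The Blinding section keeps the nurses who collect visit data unaware of allocation; the calls fall outside that protection.

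The events most exposed are those the Adverse events section names from earlier use of the diet: weakness and headache. Such symptoms are easily noted on the day and easily lost when the next scheduled question may be six months away. With the same true rate in both arms, more would be recorded under FMD.

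At stake is the reading of tolerability. The article presents the trial as the first of this diet in people with type 2 diabetes treated by their general practitioner. It provides for a yearly safety report to the ethics committee and for no data safety monitoring board. Counts of non-serious AEs by arm are likely to be read as evidence on tolerability, and part of any difference would reflect how the events were collected.

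**Working it through.** The plan gives no figure on AE ascertainment to reproduce. Its power calculation concerns the binary efficacy endpoint and has no bearing here.

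**1. Scheduled post-baseline contacts at which AEs are recorded**

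Inputs: Table 2; the call described in Data collection; monthly cycles for a year (Intervention section), taken as about 12. The number of calls is an assumption, from 1 in total to 1 per cycle.

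| | Control | FMD, 1 call | FMD, 12 calls |
|---|---|---|---|
| Non-serious AEs | 2 (T4, T8) | 2 + 1 = 3 | 2 + 12 = 14 |
| Ratio to control | 1 | 3/2 = 1.5 | 14/2 = 7 |
| Serious AEs (visits) | 8 | 8 | 8 |

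The inequality is confined to non-serious events. These are counts of opportunities, not of events.

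**2. What this could do to recorded rates**

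Assumptions, none of them from the article: equal true AE rates; a call in each of 12 cycles; 90% capture at a call; a proportion r captured by recall at T4 or T8, with r from 0.3 to 0.9; call and visit capture independent; no general practitioner reports.

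- Control capture = r
- FMD capture, if each call covers its whole month = 1 − (1 − 0.9)(1 − r)
- Rate ratio R = FMD capture / r
- If calls catch only events on the 12 × 5 = 60 diet days, with events spread evenly over the year: ratio = 1 + (60/365)(R − 1)

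| r | FMD capture | Ratio, whole month | Ratio, diet days only |
|---|---|---|---|
| 0.3 | 0.93 | 3.10 | 1.35 |
| 0.5 | 0.95 | 1.90 | 1.15 |
| 0.7 | 0.97 | 1.39 | 1.06 |
| 0.9 | 0.99 | 1.10 | 1.02 |

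The diet-days column is closer to the text, because the call takes place during the FMD period.

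**3. Sensitivity to the number of calls**

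Let q be the monthly AE probability in both arms (5% or 10%), r be 0.3 to 0.9, call capture c be 0.5 to 0.9, and d = 1 − (1 − r)(1 − c). Each call is again allowed to cover its whole month, which is generous to the calls. The share with at least one recorded AE is

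- control: 1 − (1 − qr)^12
- FMD with k calls: 1 − (1 − qd)^k (1 − qr)^(12 − k)

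With k = 12:
- q = 0.05, r = 0.9, c = 0.5: 42.5% control, 44.2% FMD, a false gap of about 2 points.
- q = 0.10, r = 0.3, c = 0.9: 30.6% control, 69.0% FMD, a false gap of about 38 points.

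With k = 1 the gap over the same grid is about 0.1 to 4.5 points.

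The direction is the same in every scenario. The size depends almost wholly on quantities that the article does not give.

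**The case against.** The strongest reply is that no planned analysis is damaged. AEs are not among the primary or secondary outcomes and no between-arm AE test is specified. Closer contact on diet days is a defensible safety measure, and a caveat under a descriptive table might be enough. This stands to the extent that the problem is a risk to a later descriptive comparison and not an error in a planned test. It does not remove the asymmetry, which the article states outright.

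A reader might infer several stronger things that the article does not support:

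- That every between-arm safety comparison is biased. Serious events are asked about at every visit on one schedule, and the T4 and T8 AE recordings are also common to both arms.
- That control events reach the team only through six-month recall. General practitioners are asked to report AEs in both arms. This softens the inequality but does not replace the calls.
- That the calls systematically question participants about AEs. Their stated purpose is compliance, and events are noted where applicable, so 90% capture may be too high.
- That the contacts are 14 against 2, or the rate ratio 3.1. Both need a call in every cycle. The ratio also needs each call to cover a whole month, 30% recall at visits and no general practitioner reports.

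It can also be said that if diet days really are symptomatic, part of any excess in the FMD arm is real. That is true. The equal-rate assumption only isolates the artefact; with unequal ascertainment, the real part and the artefact cannot be separated in the recorded counts.

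**Conclusion.** The point holds for non-serious AEs only. As written, the plan gives the FMD arm an additional, unblinded recording route timed to the diet, and a descriptive comparison of non-serious AEs would lean towards more events in that arm. Scheduled post-baseline contacts are 3 to 14 against 2, depending on whether there are 1 or 12 calls. On the assumptions shown, the apparent rate ratio at equal true rates is about 1.02 to 1.35 if calls catch only diet-day events, and higher only if they cover the whole month. The direction follows from the document; the size does not. Serious AE ascertainment is symmetric. The change is worth making because it is cheap, not because a primary conclusion is threatened.

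**What to change.** 1. In Table 2, add the non-serious AE question at T1-T3 and T5-T7, with the same wording and recall period in both arms. Both arms already attend these visits and are already asked there about serious events. Scheduled visit contacts for non-serious AEs then become 8 in each arm.
2. Record the source of each AE: visit, call or general practitioner.
3. State that the between-arm comparison of non-serious AEs uses events reported at the common visits. An event noted on a call and reported again at a visit counts in that comparison.
4. Report call-recorded events separately, as tolerability data for the FMD arm. Nothing is discarded.

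The cost is one question at six existing visits, one source field and a sentence on tabulation. Visits become slightly longer, and there is a slightly greater chance that participants disclose their allocation to the blinded nurses. That added risk is small, since AEs are already asked about at T4 and T8. For participants whose in-between visits have already passed, the source split still allows a comparison on T4 and T8.

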**Fig. 1 Fig1:**
[figure not shown]
Timeline of assessments from T0 (baseline) to T8, also in relation to the timing of the FMD

**Table 2 Tab2:** Detailed schedule of assessments during follow up

Follow up	Screening	Baseline	In the first month	In the second month	In the fourth month	After six months	In the eighth month	In the tenth month	In the twelfth month	After twelve months
		T0	T1	T2	T3	T4	T5	T6	T7	T8
**Participant characteristics**	X									
**Medical history**	X									
**Anthropometrics**	X	X	X	X	X	X	X	X	X	X
**Blood pressure**	X	X	X	X	X	X	X	X	X	X
**Medication dosage**	X	X				X				X
**Adverse Events**		X				X				X
**Serious Adverse Events**		X	X	X	X	X	X	X	X	X
**MRI**		X				X				X
**Stool sample (including registration form)**		X	X			X				X
**Finger-stick ketone bodies test**		X	X		X		X		X	
**Questionnaires**										
Cost questionnaire					X	X		X		X
Quality of Life (EQ-5D-5L)		X			X	X		X		X
Treatment satisfaction (DTSQs)		X			X	X		X		X
Treatment satisfaction (DTSQc)										X
Eating habits (DHD-FFQ)		X				X				X
Physical activity (SQUASH)		X				X				X
MRI safety questionnaire	X	X				X				X
**Fasting blood sample**										
HbA1c	X	X				X				X
Glucose	X	X	X		X	X	X		X	X
Creatinin	X									
ASAT	X									
ALAT	X									
Haemoglobin	X									
Red cell indices	X									
Leucocytes	X									
Thrombocytes	X									
OGTT (5x glucose and 5x insulin)		X				X				X
Total cholesterol		X				X				X
Low-density lipoprotein (LDL)		X				X				X
High-density lipoprotein (HDL)		X				X				X
Triglycerides		X				X				X
High sensitive CRP		X				X				X
Metabolomics		X								X
IGF-1^a^		X	X		X		X		X	
Insulin-like growth factor-binding protein (IGF-BP-1)^a^		X	X		X		X		X	

Laboratory tests with a ^a^ will only be performed in the FMD group

In compliance with the GCP guidelines, the investigator will store all source documents that support the data collected from each subject, as well as all essential study documents. Source documents include paper case report forms (CRFs), Castor EDC (eCRFs) and Hix ChipSoft (Electronic Health Records Software used in the LUMC). Participant specific data will be labelled with a study identification number and entered in the electronic trial database in Castor EDC. The study identification number will be linked to personal information of the participant used for trial logistics in a separate electronic study database, which will be safeguarded by the investigator in accordance with GCP rules.

### Outcomes

An overview of the outcomes measured at each stage of the FIT study can be found in Table 2. Height will be measured in cm. Body weight will be measured to the nearest 100 g in light clothing without shoes. Body fat percentage by Bioelectrical Impedance Analysis will be performed in the same conditions. Waist circumference will be measured in cm halfway between the point of the lowest rib and the iliac crest. Blood pressure will be measured with participants seated, an average of two measurements will be taken. For an overview of the different questionnaires used in the FIT study, see Table 2. Participants will be requested to bring a recent overview of their medication use from their GP or their pharmacy.

Finger-stick test for measurement of ketone bodies will be performed in fasting conditions. Blood will be collected in fasting conditions, for details of laboratory tests, see Table 2.

The oral glucose tolerance test (OGTT) will be performed at baseline, after 6 months and after 12 months. Participants will be asked to stop using all glucose lowering medication for 1 day prior to any OGTT. A Venflon catheter will be inserted into an antecubital vein. Participants will be asked to drink a standard solution of 75 g of glucose dissolved in 300 ml of water. Blood will be collected at time 0, 30, 60, 90 and 120 min for measurement of glucose and insulin (at all timepoints).

MRI will be performed after at least 6 hrs of water-only fasting, after verifying that there are no contraindications to perform an MRI. The MRI will take place at baseline, after 6 months and after 12 months. All imaging will be performed on an MRI system operating at a field strength of 3 Tesla (Philips Medical Systems, Eindhoven, The Netherlands). Total scan time will be around 60 min. No additional contrast or medication will be administered during the examination. Cardiovascular MRI will be performed, for which a vector electrocardiogram and a breathing registration sensor is positioned on the abdomen, and a cardiac coil is placed over the chest. Breathing instructions are given through a headset. Multiple scans will be performed to determine heart dimensions and systolic and diastolic function of the heart. Flow through the mitral, tricuspid, aortic, and pulmonary valves will be assessed. For measuring body fat distribution, the volumes of the visceral and subcutaneous fat depositions of the body trunk will be visualized and quantified. Fat distribution in liver (LiverMultiScan, Perspectum Diagnostics, Oxford, UK) and heart tissue (Custom made software patch for respiratory navigator gated 1H-MR Spectroscopy, Leiden, The Netherlands) will be determined.

Stool samples will be collected at home using provided equipment and instructions. Samples will be stored at home in their refrigerator and brought to clinic within max 2 days. After receiving the stool samples, the samples will be processed and stored at − 80 °C until further analysis.

